The participant must complete the same 16 tasks in the same order as stage 1; however, the participant must now use Taskiir to help them answer the question and to find evidence to support their answer. Evidence is collected by the participant selecting text, images, or both from the source documents they read. The time allocated to search for each task is set according to the timing cohort the participant belongs to and will be one of 3, 6, or 9 min. The participant is told of the time allocation at the start of each question and a minute-by-minute countdown timer is always visible to the participant; warnings are given 30 seconds before time-out. At time-out, the screen is blocked, and the participant is taken to the task completion screen to enter their final details. Other methods of communicating the time limit were trialed during development of the system. In the end, the above method was chosen because it provided a balance between (1) making the participant aware of the time allocated for each question, (2) avoiding time anchoring (where the participant incorrectly assumed all questions are allocated the same time as the first question), (3) keeping them updated with the time remaining so they do not run out of time without warning, and (4) not distracting the participant with time information (eg, using a second-by-second countdown timer that diverted too much attention away from the task).

As this is the first such study measuring the impact of time variation, a few time limits covering a wide range are required to generate significant differences in the outcomes. A useful starting point to establish these time limits is the average completion time of 6.1 min per question, reported in the Westbrook study [33]. From the same study, the SD, based on the average completion times for each of the 8 questions, across 2 systems, is 3.1 min. Therefore, time limits are set at the average question answer time (6 min) and approximately 1 SD either side of this (3 and 9 min). These limits should induce time pressures for 84% of questions with a 3-min time limit, 50% of questions with a 6-min time limit, and 16% of questions with a 9-min time limit. From previous studies, realistic answer timeframes for busy clinicians should be below 5 min [3,15,35], so the 3 proposed time limit cohorts will encompass this pragmatic indicator of search time suitability.

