### Task Order, System Rotation, and Task Timing

Task order and system rotation is set as per the table in Multimedia Appendix 4 for each participant to minimize confounding factors. The design is as follows:

A Latin square experimental design is constructed for 16 tasks and 16 participants to minimize the impact of user fatigue on specific tasks.To minimize task order effects, each column of the square is randomized.To incorporate a within-subject design across the system variable, 2 sets of the Latin square derived in (2) are required with alternating use of systems. The first tranche of 16 participants will start their first task with the state-of-the-art system, whereas the second tranche will start with BM25 system. In this way, across the 32 participants, each system will be used equally across all tasks and will experience the same task-order pattern.

The search time allowed for each task is controlled by applying a time limit for each task the participant performs. Participants are randomly assigned to 1 of 3 timing cohorts. The time constraint by task number is specified for each cohort in Multimedia Appendix 5. The rotation of task timing ensures that:

the maximum duration for search in stage 2 is fixed to 96 min for all participantseach task is conducted under all time constraints an equal number of times (32 per cohort)a within-subject design across the time constraint variable such that each participant performs 4 to 6 tasks per time constrainttask time constraints are applied in the same random order according to the task order rotation Latin square, specified above

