### Statistical Analyses

To assess the impact of introducing the SML search system on clinical decision quality (RQ-1), each participant’s answer, both presearch and postsearch, will be coded to right (R) or wrong by comparing the participant’s answer with an expert judged assessment (gold answer) of each task. Samples for which (1) no evidence is captured and (2) no relevant documents are marked (either as essential or helpful), by the participant for their postsearch answer, will be discarded, as the value of the search system cannot be confirmed in these cases. Therefore, the decision quality is defined by the correct answer rate (number of right answers/total sample count (N)). A further detailed analysis will be performed of the collected evidence to identify tasks where the literature may contradict the gold answers. Where this occurs, the task answers will be reviewed by experts and overall correct rates adjusted.

To assess the significance of any change in the proportion of right or wrong answers, the McNemar test will be employed because it is a nonparametric test suited to a binary result, with samples taken at 2 points in time. Nonparametric is a better model to assume, given that the data distribution is unlikely to be regular because of the different medical groupings of participants. The sign test, which is also a nonparametric test, will be used to identify any significant changes to the correct rate. To assess any differences between the participant groups (nurses, doctors, and students), a Chi-square analysis will be performed. The participant’s confidence in their answers will be assessed presearch and postsearch to identify any significant changes relating to search intervention, also using chi-square analysis.

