To assess the impact of search engine performance on clinical decision quality (RQ-3), a similar set of analyses will be performed as that for RQ-1, except broken down by search system (state-of-the-art and BM25). In addition, the same ANOVA methods employed for time-constraint categories in RQ-2 analysis will be performed. In addition, an ANOVA will be performed across system categories and system time constraints to identify cases where system performance effects may matter most. The impact of search engine performance on clinical decision time (RQ-3) will also be assessed by evaluating the postsearch task completion times for those tasks that were completed (ie, relevant documents and/or evidence identified). This is measured in 2 ways: (1) search time only and (2) search time plus time spent filling in the answer form. Differences in search times between the systems will be assessed using the chi-square analysis. Finally, a participant-derived performance assessment of the 2 systems can be constructed by building a graded query relevance (QREL) listing (standard format for representing relevance assessments in IR), by query, based on all participants’ relevance ratings. Using this QREL, a recomparison of the 2 systems can be evaluated and compared using the formal TREC evaluation results to provide better insight into any changes observed (or not) in the clinical decision and timing results for the 2 systems.

There are a number of potentially confounding factors within the experimentation. A covariant analysis (repeated measure ANOVA) will be performed on the task number, task at total duration point (for fatigue), and time transitions (eg, 3-min task to 6-min task and 3-min task to 9-min task).

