## Appendix

Multimedia Appendix 1 Pre-task questions and answer options.

Multimedia Appendix 2 Post tutorial instructions provided to the user prior to task assessment.

Multimedia Appendix 3 User interaction time capture . Taskiir user-interaction data capture detail for Stage two of the study, when the participant can use a search engine to help them to complete their task. Column 2 identifies all captured variables as either time-stamped events or calculated variables. Column 3 identifies where the event is triggered or how the variable is calculated.

Multimedia Appendix 4 Task Presentation Order : Latin square design of task presentation order. The presentation order is from left to right. The numbers in the table represent the task numbers. The subjects are denoted in the first column from S1 to S16. Two such squares (32 subjects) form a timing cohort. System selection is alternated for each column of the square starting with the State of Art system in column one. Note that the task order for the first 16 subjects are the same as for the second 16 subjects, however the search system used for each task is switched, i.e., so that the BM25 system is used for column 1 questions.

Multimedia Appendix 5 Task timing selection for each question. Timing cohorts of 32 people are identified in the top row as C1, C2 and C3. Each cohort will conduct the search for each task, as listed in the first column (T1, T2...T16), within the time constraint specified in minutes in the table.

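### The repeated-measures ANOVA planned for order, fatigue and time transitions does not suit a rotation that leaves transitions unbalanced

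*Protocol article*

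**What the plan says.** The last paragraph of Statistical Analyses acknowledges possible confounding and gives one analysis for it: "A covariant analysis (repeated measure ANOVA) will be performed on the task number, task at total duration point (for fatigue), and time transitions". The examples of a transition are "eg, 3-min task to 6-min task and 3-min task to 9-min task". None of the other planned tests (McNemar, sign, chi-square, ANOVA by limit and by system) is described as adjusting for these factors.

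The design itself deals with order and fatigue. Task Order, System Rotation, and Task Timing states: "A Latin square experimental design is constructed for 16 tasks and 16 participants to minimize the impact of user fatigue on specific tasks", and then: "To minimize task order effects, each column of the square is randomized". Participants are randomised to three timing cohorts. The limit for each task is set by cohort; the note on Multimedia Appendix 5 reads "Each cohort will conduct the search for each task, as listed in the first column (T1, T2...T16), within the time constraint specified". The order in which a participant meets the limits therefore follows from the task order. Total stage 2 search time is fixed at 96 min, and "each participant performs 4 to 6 tasks per time" limit. Nothing in that section balances which limit follows which.

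Earlier in Statistical Analyses, under RQ1, postsearch answers with neither captured evidence nor a document marked relevant "will be discarded, as the value of the search system cannot be confirmed in these cases".

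**The concern.** Classical repeated-measures ANOVA compares levels within each participant and drops anyone who lacks a level. The time-transition factor is the one that the rotation leaves to chance, so it is also the one for which this analysis is the only protection. If a sizeable share of participants never meet some transitions, the analysis rests on the subset whose random sequence happened to contain them all. A finding of no transition effect would then carry little weight. Two further features fit poorly: a first task has no preceding limit, and the duration point is a quantity that varies with each participant's sequence, not a set of levels shared by all.

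**Working it through.** **The plan's own figure.** The document gives no figure for how complete this ANOVA would be, so there is none to reproduce. The sample size is not at issue: for 40% v 50%, 90% power and two-sided 5%, (1.960 + 1.282)² × (0.4×0.6 + 0.5×0.5) / 0.1² = 514.9, which agrees with the stated 514.

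**Step 1: tasks per limit.** Let a, b, c be a participant's tasks at 3, 6 and 9 min. Then a + b + c = 16 and 3a + 6b + 9c = 96. Dividing the second by 3 gives a + 2b + 3c = 32. Subtracting twice the first gives c = a, so b = 16 − 2a. With 4 to 6 tasks per limit, only 5/6/5 and 6/4/6 remain. Each task is used equally often under each limit, so the three cohorts together hold 16 tasks at 3 min: 5 + 5 + 6. Two cohorts are 5/6/5 and one is 6/4/6.

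**Step 2: transitions available.** Stage 2 keeps all the tasks ("The participant must complete the same 16 tasks in the same order as stage 1"), so each participant has 16 − 1 = 15 consecutive pairs. There are 3 × 3 = 9 ordered types if same-limit pairs count, and 6 if only changes of limit count.

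**Step 3: share with every type, before any discard.** Multimedia Appendices 4 and 5 are not shown, so this was simulated. The first two rows of the table use random orders of each mix (40,000 per mix). The third uses 500 designs built from a cyclic 16×16 Latin square with its columns permuted and a random task-to-limit map meeting the constraints above.

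| Basis | All 9 ordered types | All 6 changes of limit |
|---|---|---|
| 5/6/5 | 40% | 65% |
| 6/4/6 | 27% | 59% |
| Latin square, three cohorts | 35% | 63% |
| 95% range over designs | 21% to 48% | 48% to 77% |

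The first two rows agree with the third: (2 × 0.399 + 0.266)/3 = 0.355 and (2 × 0.648 + 0.588)/3 = 0.628. Of 96 participants, about 96 × 0.355 = 34 have all 9 types and 96 × 0.628 = 60 have all 6. The incomplete shares are therefore about 65% and 37%. If direction is ignored (3 unordered changes), about 97% are complete.

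**Step 4: duration point.** After five tasks, the search time allotted so far could be as little as 5 × 3 = 15 min or as much as 5 × 9 = 45 min, depending on the sequence. Participants at the same position do not share a common duration level unless the variable is binned.

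**Step 5: discards, if the rule applies here.** With an assumed independent discard probability d per answer, the chance of keeping all 16 is (1 − d)^16.

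| Assumed d | All 16 kept | Of 96 | All 9 types | All 6 changes |
|---|---|---|---|---|
| 1% | 85% | 82 | 34% | 62% |
| 5% | 44% | 42 | 29% | 56% |
| 10% | 19% | 18 | 22% | 48% |

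At d = 10%, a complete-case analysis by task number keeps about 17.8 × 16 = 285 answers. A model that accepts incomplete participants keeps about 0.9 × 96 × 16 = 1,382 of 1,536.

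**The case against.** The other side has several good points.

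- A reader might infer that order, fatigue and transitions are otherwise uncontrolled. They are not. The Latin square, the randomised columns, the alternation of systems and the random cohort assignment act on order and fatigue by design. Only the transitions lack such a control.
- A reader might infer that most participants cannot enter the analysis. On transitions alone, that needs same-limit pairs to count. The protocol's only examples are changes of limit, and on that reading a majority (about 63%) are complete before discards. They fall below half only near an assumed 10% discard rate.
- A reader might object that each participant fills only 16 of 16 × 3 = 48 task-by-limit cells. That is true, but the sentence does not list time limit as a factor in this ANOVA or put all terms in one model, so it describes an analysis nobody has proposed.
- The discard rule is written for RQ1. It is not extended in words to this analysis, it requires both conditions, and no rate is given. Before discards, every participant who finishes has all 16 task values. Clustering of discards within participants would leave more of them complete.
- Outcome, factor coding and missing-data rules may properly sit in a fuller document, and the term covariant analysis leaves some room about the model.

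These points limit the size and wording of the criticism. They do not remove the mismatch: the named method calls for complete within-subject levels, and the stated rotation does not supply them for transitions.

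**Conclusion.** The concern holds in a limited form. The repeated-measures ANOVA is the only planned analysis adjustment for order, fatigue and time transitions, though not the only control. For transitions, roughly a third (6 types) to two thirds (9 types) of participants would be incomplete before any answer is lost. The size rests on the classical complete-case form of the method, on the definition of a transition, and on simulated orders standing in for appendices that are not shown. If only unordered changes were meant, the problem would nearly vanish. The loss on task number is conditional on the discard rule applying and on a rate the document does not give. This is a weakness in a supporting analysis, worth correcting. It does not touch the sample size or the stated tests for RQ1 to RQ3.

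**What to change.** In the last paragraph of Statistical Analyses, replace the repeated-measures ANOVA with an answer-level mixed model: logistic for right or wrong, linear for ratings and times. Use random intercepts for participant and for task. Use fixed effects for time limit, system, the previous task's limit (none, 3, 6 or 9 min), and either position (1 to 16) or cumulative search time. Both of the last two are not necessarily needed, because they are strongly correlated. Add a previous-by-current limit interaction, since main effects alone do not estimate the specific transitions named. Across 96 participants there are 96 × 15 = 1,440 transitions, an average of 1,440 / 9 = 160 per ordered type, all usable without requiring any one participant to have every type. First tasks get a defined level.

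The cost is a paragraph of wording and slightly more modelling work, plus the usual distributional assumption for the random effects. No new data are needed.

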## Results

Recruiting began for the study in June 2018. As of April 4, 2019, there were 69 participants enrolled. The study is expected to close by May 30, 2019, with results to be published in July 2019.

## Discussion

The study is currently underway, and results will be reported at the conclusion of participant testing.

## Appendix

Multimedia Appendix 1 Pre-task questions and answer options.

Multimedia Appendix 2 Post tutorial instructions provided to the user prior to task assessment.

Multimedia Appendix 3 User interaction time capture . Taskiir user-interaction data capture detail for Stage two of the study, when the participant can use a search engine to help them to complete their task. Column 2 identifies all captured variables as either time-stamped events or calculated variables. Column 3 identifies where the event is triggered or how the variable is calculated.

Multimedia Appendix 4 Task Presentation Order : Latin square design of task presentation order. The presentation order is from left to right. The numbers in the table represent the task numbers. The subjects are denoted in the first column from S1 to S16. Two such squares (32 subjects) form a timing cohort. System selection is alternated for each column of the square starting with the State of Art system in column one. Note that the task order for the first 16 subjects are the same as for the second 16 subjects, however the search system used for each task is switched, i.e., so that the BM25 system is used for column 1 questions.

Multimedia Appendix 5 Task timing selection for each question. Timing cohorts of 32 people are identified in the top row as C1, C2 and C3. Each cohort will conduct the search for each task, as listed in the first column (T1, T2...T16), within the time constraint specified in minutes in the table.

## Abbreviations

ANOVA: analysis of variance
CDS: clinical decision support
DCG: discounted cumulative gain
IR: information retrieval
MAP: mean average precision
nDCG: normalized discounted cumulative gain
QREL: query relevance
RQ: research question
R-prec: R-precision
SERP: search engine results page
SML: scientific medical literature
TREC: text retrieval conference
UMLS: Unified Medical Language System
